**Discussion:**

The results of this study may be translated to clinical practice, incorporating a specific autonomy recovery programme into comprehensive rehabilitation programmes of care for cancer patients with asthenia. The current study addresses to improve the conventional clinical practice by proposing a multimodal physical exercise and functional rehabilitation program intervention, which will be implemented by an interdisciplinary team, to try to improve the autonomy of cancer patients with cancer-related asthenia.

**Trial registration:**

ClinicalTrials.gov; ID: NCT04761289. (February 18, 2021). https://clinicaltrials.gov/ct2/show/ NCT04761289.

## Background

Nowadays, we observe an exponential increase in the five-year survival of patients with cancer, this is due to the improvement in preventive strategies as well as the greater knowledge about the oncologic pathology. Related to this higher life expectancy in cancer patients, an increase in the side effects of the treatments administered to surviving patients has also been observed [1]. These are mainly due to the increase in the lines of treatment employed. This increase produces a deterioration in the functionality and in the quality of life of the patients [2]. Some of these side effects include cancer-related asthenia, depression and dyspnoea [3]. Cancer-related asthenia is the most common symptom associated with cancer and its treatment, and it strongly impacts patient quality-of-life parameters [4]. However, this problem is still generally underestimated by many professionals in the field of oncology [5].

Patients with tumour asthenia often experience fatigue, which makes their daily lives difficult. In addition, the presence of fatigue is usually associated with alterations in body composition such as loss of muscle mass or an increase in visceral fat [6].

Among the intervention measures currently available to address this problem, the National Comprehensive Cancer Network (NCCN) expert panel considers educational measures, controlled therapeutic physical exercise, and energy conservation techniques as fundamental, always when undertaken within a complete functional rehabilitation program [7]. There is scientific evidence that asthenia can be better controlled after the implementation of non-pharmacological measures, especially controlled physical exercise [8, 9]. In addition, physical exercise has also been shown to mitigate the afore mentioned alterations in body composition that usually occur in cancer patients [10, 11]. Indeed, Fernández-Lao et al. showed that patients with breast cancer who performed a multimodal physical exercise program achieved a reduction in body fat and an increase in lean body mass [12].

The available scientific literature indicates that the efficacy of these physical exercise interventions to address cancer-related fatigue is increased when a psychological component is added, especially when a interdisciplinary (oncology, nursing, physiotherapy, occupational therapy, and medicine) biopsychosocial approach is taken [13, 14]. Thus, different aspects related to loss-of-function, pain, and fatigue associated with fear-avoidance disorders should also be explored and evaluated by testing the degree of kinesiophobia in patients with cancer [15]. The cognitive-behavioural model of fear of movement notes that patients with chronic pain or fatigue syndrome tend to avoid physical activity because they believe that this activity causes or exacerbates these symptoms; avoidance behaviour leads to even greater fear and symptoms, producing more pain or fatigue [15–17].

These factors can be extended to patients with cancer-related asthenia, which is why physical activity is important to help them avoid loss-of-function and reduced physical capacity [15]. Selection of the optimal intervention environment is based on clinical complexity and the patient’s ability to self-manage their situation. Several previous studies, including a meta-analysis of 14 randomised controlled clinical trials in breast cancer survivors with an intervention supervised by phone or email [18], have shown that supervised physical exercise interventions outside the healthcare provision environment, both in the community and at home, have had good results.

However, despite the potential benefits of such interventions, there is little evidence available on the possible effects that multimodal physical exercise and functional rehabilitation programs may have on patients with cancer-related asthenia outside healthcare settings. Thus, this present clinical trial was designed to address this research gap and to create empirical evidence regarding the effect of an interdisciplinary multimodal physical exercise and functional rehabilitation program intervention applied at the time of hospital discharge in patients with cancer-related asthenia.

From the above, we are proposing as an intervention a multimodal physical exercise and functional rehabilitation programme, implemented by an interdisciplinary team established by nurses, occupational therapists, physiotherapists, and specialist doctors, will improve the autonomy of patients with cancer-related asthenia. It would be a reeducation in the completion of the activities of daily living, so as to foment the recovery of personal autonomy. The findings will provide important insight into the development of an effective care model with a comprehensive rehabilitation programme that includes a specific autonomy recovery programme in oncological patients with asthenia. Taking into account the results obtained in our clinical practice in the Oncology Hospitalisation Unit at the University Hospital Complex of Salamanca (CAUSA), we consider important the implementation of specific clinical care protocols for this type of cancer patients, and its study through clinical trials.

## Methods/design

### Design and aims

This experimental, prospective, randomized, parallel-controlled clinical trial, with two arms of fixed assignment with an experimental and a control group, will be conducted during a year in the Oncology Hospitalisation Unit at the CAUSA. We will use consecutive sampling to select the participants with oncological asthenia who are hospitalised at the time of inclusion.

This is one of the clinical trials that are starting in our Unit, with an interdisciplinary care team, and similar design, patients and procedures with others, such us the recent study protocol published [19].

According to the background, the primary aim of this study is to assess the effects of a multimodal physical exercise and functional rehabilitation program on fatigue, pain, functional capacity, and quality of life in cancer patients with cancer-related asthenia. The objectives are focused to compare the effects produced by the implementation of a multimodal physical exercise and functional rehabilitation program, with an isolated intervention using standard clinical practice treatment.

### Sample/participants

Participants: The patients will be recruited from the Oncology Hospitalisation Unit at the CAUSA when they will be hospitalised. The Unit’s investigators will invite patients to participate in the study by explaining the details of the clinical trial, and they can then be included once they have given their verbal and written consent, and meet the following selection criteria: (A) Inclusion criteria: Participants must have a pathological diagnosis of an oncological disease, be over 18 years of age, be hospitalised at the time of recruitment in the Oncology Hospitalisation Unit at the CAUSA, having a score of 15–55 points on the Barthel Index (BI), having a score of 4 or more on the visual-analogue scale (VAS) for cancer-related asthenia and have signed an informed consent form indicating voluntary agreement to participate in the study. (B) Exclusion criteria: not having an adequate cognitive state to be able to comprehend and follow the orders provided (fewer than 23 points on the Mini Mental State Examination, MMSE), and having a haemoglobin level lower than 10 g/dL. (C) Withdrawal criteria: disease progression which brings the patient to a terminal situation or to death, and non-completion of the follow-up and final assessments.

Assignment, randomisation and blinding: After recruitment, individuals will be assigned by a randomisation process to one of two study groups: Experimental Group or Control Group. Detailed in Fig. 1.

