**Fig. 1 Fig1:**
[figure not shown]
Study design. The enrolled participants will be randomly assigned to one of the study groups and will be assessed at three pre-specified time p

We will employ a simple randomisation process that consists of generating a table of random numbers of the same size as the estimated study sample with Microsoft Excel 2020 to assign subjects to each of the study groups. For even numbers, the subject will be assigned to the Experimental Group, and for odd numbers, the subject will be assigned to the Control Group. Randomisation, recruitment and assignment of subjects to each group will be performed by research staff not involved in the evaluations or interventions in each group, which will avoid potential bias in the study.

The participating subjects will not be blinded, due to the specific characteristics of the intervention in each group. However, the researchers responsible for the study measurements and statistical analysis will be blinded, with the intention of avoiding any contamination between groups, thus increasing the rigour of the study process.

Sample size: The sample size has been estimated based on the potential modification of one of the main outcome of the study—the score on the Barthel Index. For this calculation, we have considered the results obtained in a similar, where a modification of 17 points in the BI score was obtained, as a difference attributable to the intervention, considering this as the difference between the modification of the experimental group and the control group [20]. With these premises, accepting an alpha risk of 0.05 and a beta risk of 0.2 in a bilateral contrast, with 50 individuals (25 subjects in the experimental group and 25 in the control group, the statistical power was 90 % to recognize as statistically significant a change of 17 points between both groups in the BI score. The sample size was estimated using the programme EPIDAT 4.2.

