### Procedures and data collection

#### Evaluations and study plan

Participants will be assessed at three points during the study: Firstly, the baseline assessment at the beginning, the second assessment after seven days, and a third final assessment, before the patients are discharged from hospital. The baseline assessment will be performed after recruitment and before randomisation and assignment of subjects to the corresponding group. This initial assessment includes the recording of the independent variables and the primary and secondary outcome variables of the study. Then, after randomisation, the corresponding intervention will begin to be applied to each group. Subsequently, the other further assessments will be carried out, one after seven days, considered as the follow-up assessment, and another at hospital discharge, considered as the final assessment. This can be seen in more detail in Table 1.

**Table 1 Tab1:** Timeline and dimensions assessed at the time points

	STUDY PERIOD							
	**Enrolment**	**Allocation**	**Post-allocation**					**Close-out**
**TIMEPOINT**	***Month 1-2***	***Month 2-3***	***M4***	***M5***	***M6***	***M7***	***M8***	***M9-M12***

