#### Work plan and visit structure

Once the possible study candidates have been identified in the Oncology Hospitalisation Unit at the CAUSA, an interview with each individual will be organised to explain the purpose of the study to them and thereafter, invite them to sign the informed consent to their participation. Each participant will complete 3 planned evaluation visits. One at baseline, prior to randomisation, and two follow-up visits 15 days and 1 month after the first visit. The structure of all three 3 visits will be the same and each will last approximately one hour. In addition, there will be a telephone follow-up 3 and 6 months after the randomisation. The study variables will be evaluated during these visits, as specified in Table 1.

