### Data analysis

The statistical analysis will be carried out on an intention-to-treat basis. The characteristics of the population will be presented as means and standard deviations for continuous variables and as a frequency distribution for qualitative variables. To assess comparability of the two study groups at the baseline, the means between both groups will be compared using chi-square tests for qualitative variables and Student t-tests for qualitative variables. The effect of the intervention on the study variables will be evaluated using a repeated measures ANOVA with two study factors: time * group. Subgroup analyses will be carried out considering certain variables and/or categories from the baseline evaluation such as age or the initial FACT scale score. For hypothesis testing, an alpha risk of 0.05 will be set as the limit for tests of statistical significance. We will use SPSS software (version 23.0; IBM Corp., Armonk, NY) for all the statistical analyses.

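### Withdrawal for terminal progression, death or missed assessments, combined with repeated-measures ANOVA, would turn the stated intention-to-treat analysis of the Barthel Index into a completers analysis

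*Protocol article*

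**What the plan says.** Sample/participants, item (C), gives the withdrawal criteria as "disease progression which brings the patient to a terminal situation or to death, and non-completion of the follow-up and final assessments". Under Evaluations and study plan, "The baseline assessment will be performed after recruitment and before randomisation and assignment of subjects to the corresponding group". These criteria therefore act on patients who have already been randomised.

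Data analysis makes three relevant statements:
- Analysis set: "The statistical analysis will be carried out on an intention-to-treat basis".
- Model: the effect of the intervention is to be "evaluated using a repeated measures ANOVA with two study factors: time * group".
- Software: "We will use SPSS software (version 23.0; IBM Corp., Armonk, NY) for all the statistical analyses".

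Work plan and visit structure says "Each participant will complete 3 planned evaluation visits", one at baseline and two afterwards. The article gives two different timings for the later two (seven days and discharge, or 15 days and one month), but three assessments either way. On blinding, Sample/participants says "The participating subjects will not be blinded, due to the specific characteristics of the intervention in each group".

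The text shown does not say whether withdrawn patients stay in the analysis, and the sample size of 25 per arm includes no stated allowance for loss.

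**The concern.** Intention to treat means that every randomised patient is analysed in the allocated arm. Here a missed assessment is itself a ground for withdrawal, which works as a completer rule. Death and terminal progression are also listed, and both are closely tied to the main variable, dependence in daily living. The patients are in hospital with a Barthel score of 15 to 55 at entry, so those lost would tend to be those who do worst.

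The named model points the same way. A standard repeated-measures ANOVA needs a score at every time point, so one missed assessment removes the patient's other scores as well.

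Two things are at stake. If loss differs between the arms, which is possible when patients know their allocation and only one arm has a daily exercise programme, the Barthel contrast is biased. If loss is equal, the contrast may be roughly unbiased for completers, but it no longer describes all randomised patients and power falls.

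**Working it through.** **Step 1. The two readings of withdrawal.**
- *Withdrawal means leaving the analysis.* Item (C) then contradicts the intention-to-treat statement directly.
- *Withdrawal means leaving study procedures only.* The analysis set is then nominally all randomised patients, but the repeated-measures ANOVA in its standard SPSS form deletes any patient who lacks a time point.

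Both readings end with completers. As an illustration, if 10% to 20% of patients miss each of the two later assessments independently, the share left is 0.90² = 81% to 0.80² = 64%.

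**Step 2. The SD implied by the plan.** The article states 25 per arm, a 17-point difference, two-sided alpha 0.05, beta 0.2 and 90% power. It gives no SD, so the 90% cannot be reproduced and the SD has to be back-solved.

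For a two-sample t-test with n per arm, the noncentrality is 17 / (SD × √(2/n)) on 2n − 2 degrees of freedom. At n = 25:
- 90% power requires SD ≈ 18.2 (18.17; noncentrality 17 / (18.17 × 0.2828) = 3.31).
- 80% power (beta 0.2) requires SD ≈ 21.0 (21.02; noncentrality 2.86).

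A normal approximation gives 18.5 and 21.5.

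**Step 3. Power among completers.** Same formula with n = 25 × (1 − loss). The loss rates are assumptions.

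| Loss per arm | n per arm | Power, SD 18.2 | Power, SD 21.0 |
|---|---|---|---|
| 0% | 25 | 90% | 80% |
| 20% | 20 | 82% | 70% |
| 30% | 17.5 | 77% | 64% |

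**Step 4. Bias with no true effect.** Let outcomes be normal with the same mean in both arms, and let a share d of an arm be lost according to a score that has correlation ρ with the outcome (poorer outcomes lost more often). The mean of those remaining is raised by ρ × SD × φ(z_d) / (1 − d), where z_d is the d-quantile of the standard normal distribution and φ its density.
- d = 30%: φ(−0.524) / 0.70 = 0.3477 / 0.70 = 0.4967.
- d = 15%: φ(−1.036) / 0.85 = 0.2332 / 0.85 = 0.2743.
- Difference: 0.2224.

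The spurious difference is ρ × SD × 0.2224. With SD 18.17:
- ρ = 0.5: 2.0 points (12% of 17).
- ρ = 0.8: 3.2 points (19%).
- ρ = 1: 4.0 points (24%).

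With SD 21.02 the range from ρ = 0.5 to 1 is 2.3 to 4.7 points. The arm that loses more patients looks better. With the same d and ρ in both arms, the two terms cancel and the expected difference is zero.

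**The case against.** The strongest reply is that item (C) never says withdrawn patients are excluded, replaced or deleted. It may only describe how follow-up ends, since a patient who has died cannot attend a visit, while Data analysis settles who is analysed. The handling of missing scores and deaths is also commonly left to an analysis plan, which is not shown.

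The first part stands as a matter of wording: a reader might infer that the article orders withdrawn patients out of the analysis, and it does not. It does not rescue the plan, because the named model in its standard form drops the same patients and no text shown provides for incomplete ones. The second part does not answer the point, which is not about a missing imputation rule. The withdrawal criteria, the analysis principle and the model are all stated, and they do not fit together.

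Three stronger readings are also tempting:
- *Any progression leads to withdrawal.* Only progression to a terminal situation or to death is listed.
- *The result is bound to be biased.* Bias in the contrast needs loss that differs between arms, in amount or in its link to outcome. The article gives no attrition figures, and plausible loss depends on which of its two visit schedules applies.
- *The bias would be about 4 points.* That figure needs loss fully determined by outcome, whereas a missed visit can have many causes.

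**Conclusion.** The concern holds in this form: followed as written, the plan would give a completers analysis of the primary Barthel outcome under an intention-to-treat label. That conclusion rests on the stated criteria and the standard behaviour of the named model. It needs no assumed figure.

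The size does rest on assumptions. With SDs back-solved from the plan's own power figures, losing 20% to 30% per arm leaves power of about 82% to 77% (SD 18.2) or 70% to 64% (SD 21.0). Unequal loss of 30% and 15% would create a difference of about 2.0 to 4.0 points at SD 18.2, or 12% to 24% of the 17-point target. Equal loss would create roughly none. This should be settled before any data are analysed.

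**What to change.** 1. In Sample/participants, item (C), delete the second criterion, on not completing the later assessments.
2. State that meeting a withdrawal criterion removes a patient neither from the intention-to-treat set nor from outcome collection wherever assessment is still possible. This concerns data and analysis only and says nothing on when the intervention should stop.
3. In Data analysis, replace the repeated-measures ANOVA with a likelihood-based mixed model for repeated measures on all available Barthel scores, with visit and group-by-visit terms. Keep baseline as a response with a common mean for both arms. If baseline were a covariate instead, patients with no later score would drop out again.
4. Report deaths and losses by arm. The mixed model assumes that scores are missing at random and implicitly models scores after death, so prespecify a sensitivity analysis for death. Scoring Barthel 0 after death is one option among several.

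The cost is a few sentences of protocol wording, continued assessment of withdrawn patients where possible, and slightly more analysis work. The named software fits the model through SPSS MIXED.

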**Fig. 1 Fig1:**
[figure not shown]
Study design. The enrolled participants will be randomly assigned to one of the study groups and will be assessed at three pre-specified time p

We will employ a simple randomisation process that consists of generating a table of random numbers of the same size as the estimated study sample with Microsoft Excel 2020 to assign subjects to each of the study groups. For even numbers, the subject will be assigned to the Experimental Group, and for odd numbers, the subject will be assigned to the Control Group. Randomisation, recruitment and assignment of subjects to each group will be performed by research staff not involved in the evaluations or interventions in each group, which will avoid potential bias in the study.

The participating subjects will not be blinded, due to the specific characteristics of the intervention in each group. However, the researchers responsible for the study measurements and statistical analysis will be blinded, with the intention of avoiding any contamination between groups, thus increasing the rigour of the study process.

Sample size: The sample size has been estimated based on the potential modification of one of the main outcome of the study—the score on the Barthel Index. For this calculation, we have considered the results obtained in a similar, where a modification of 17 points in the BI score was obtained, as a difference attributable to the intervention, considering this as the difference between the modification of the experimental group and the control group [20]. With these premises, accepting an alpha risk of 0.05 and a beta risk of 0.2 in a bilateral contrast, with 50 individuals (25 subjects in the experimental group and 25 in the control group, the statistical power was 90 % to recognize as statistically significant a change of 17 points between both groups in the BI score. The sample size was estimated using the programme EPIDAT 4.2.

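### Even/odd simple randomisation does not secure the 25 per arm used for the power figure, and baseline Barthel is neither balanced by design nor adjusted for; the power cost is small

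*Protocol article*

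**What the plan says.** In the Sample/participants section, the assignment text after Fig. 1 sets the method: "We will employ a simple randomisation process that consists of generating a table of random numbers of the same size as the estimated study sample". The rule follows: "For even numbers, the subject will be assigned to the Experimental Group, and for odd numbers, the subject will be assigned to the Control Group". No block, stratum or other restriction is mentioned.

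The sample size paragraph directly below states power "with 50 individuals (25 subjects in the experimental group and 25 in the control group", at 90%, "to recognize as statistically significant a change of 17 points between both groups in the BI score". The 17 points is a difference in change, "considering this as the difference between the modification of the experimental group and the control group". The error rates are given as "accepting an alpha risk of 0.05 and a beta risk of 0.2 in a bilateral contrast". No standard deviation is reported.

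Elsewhere, eligibility limits baseline Barthel to 15–55 (Sample/participants). Outcomes are measured at baseline before randomisation (Evaluations and study plan). The effect is to be tested with a repeated measures ANOVA on time and group (Data analysis).

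**The concern.** The allocation rule and the power statement describe different designs. Parity of independent random numbers amounts to a fair coin toss per patient, so arm sizes are random. The power figure treats them as fixed at 25 and 25. What is at stake is whether the trial that is run matches the one described, and whether precision is lost.

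A second question is whether anything in the design or analysis limits chance differences in baseline Barthel. In a trial of 50, such a difference could be noticeable. The variable is in hand before randomisation, so it could be used in the list, the model or both.

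**Working it through.** **Inputs.** From the protocol article: N = 50, probability 0.5 per arm, difference 17 points, two-sided alpha 0.05, power stated as 90% alongside beta 0.2, baseline Barthel 15–55. Assumed: the SD of Barthel change and the SD of baseline Barthel.

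**1. The stated power.** Without an SD, the 90% can be neither reproduced nor refuted. The SD it needs at 25 per arm can be back-solved. Normal approximation: SD = 17 / ((z₀.₉₇₅ + z_power) × √(2/25)).
- 90% power: 17 / ((1.960 + 1.282) × 0.2828) = 18.5; with the noncentral t, 18.2.
- 80% power (beta 0.2): 17 / ((1.960 + 0.842) × 0.2828) = 21.5; with the noncentral t, 21.0.

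Both readings are carried forward.

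**2. Arm sizes under the parity rule.** The experimental arm size is Binomial(50, 0.5), so P(25/25) = C(50,25)/2⁵⁰ = 0.112, about one trial in nine.

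**3. Power at each split.** Noncentral t on 48 df, with noncentrality 17 / (SD × √(1/n₁ + 1/n₂)):

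| Split | P(this split or worse) | Power, SD 18.2 | Power, SD 21.0 |
|---|---|---|---|
| 25/25 | – | 90.0% | 80.0% |
| 22/28 | 48.0% | 89.6% | 79.4% |
| 20/30 | 20.3% | 88.8% | 78.4% |
| 18/32 | 6.5% | 87.5% | 76.7% |
| 15/35 | 0.7% | 84.4% | 72.8% |

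Averaged over all splits, Σ C(50,k)/2⁵⁰ × power(k, 50 − k), power is 89.4% and 79.2%. The average loss is 90.0 − 89.4 = 0.6 points, or 80.0 − 79.2 = 0.8. At 18/32 it is 2.5 or 3.3 points.

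The loss is small because precision depends on 1/n₁ + 1/n₂. A 20/30 split is as informative as 4 × 20 × 30 / 50 = 48 patients equally divided; an 18/32 split, as 4 × 18 × 32 / 50 = 46.

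**4. Chance imbalance in baseline Barthel.** SE of the baseline mean difference = SD × √(1/n₁ + 1/n₂), which is 0.283 SD at 25/25 and 0.289 SD at 20/30. The upper assumed SD, 12.9, is that of a uniform distribution over 15 to 55 in 5-point steps.

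| Assumed baseline SD | P(difference > 5), 25/25 | P(difference > 5), 20/30 |
|---|---|---|
| 8 | 2.7% | 3.0% |
| 10 | 7.7% | 8.3% |
| 12.9 | 17.1% | 17.9% |

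Forcing equal arms barely moves these figures.

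**5. What the planned analysis does with it.** The time by group term compares changes, so the raw baseline difference drops out. If follow-up regresses on baseline with slope b, a baseline difference d still shifts the contrast in change by (1 − b) × d in size. Illustration, with b assumed between 0.3 and 0.8 and d = 5: the shift is 0.7 × 5 = 3.5 down to 0.2 × 5 = 1.0 points, or 21% to 6% of the 17-point target. A model with baseline as covariate removes it.

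**The case against.** The strongest reply is that nothing here does real damage. Simple randomisation is valid and the least predictable scheme. Equal arms in a power formula are a planning convention, and the average cost is under one point of power. On the SD that 90% power implies, even 15/35 keeps power above the 80% that beta 0.2 implies. This stands, and it rules out one tempting inference: that the rule leaves the trial underpowered.

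A reader might also infer that the rule will unbalance baseline Barthel. It will not. It permits chance imbalance and does not cause it systematically. The eligibility range limits the spread, and the analysis of change removes the raw difference. What remains is that the plan does not adjust for baseline.

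A third reply is that a table of 50 random numbers could be a permutation of 1 to 50, which has exactly 25 even numbers. The text does not say so, and simple randomisation ordinarily means independent draws. The mention of fixed assignment under Design and aims is not explained as fixed arm sizes either. If a permutation is meant, one sentence would settle it.

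Finally, restriction is not free. With participants unblinded and the same staff group recruiting, randomising and assigning, a restricted list is somewhat predictable near its end. That is a reason for concealment; it does not make 25/25 the outcome of the parity rule.

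**Conclusion.** The point holds in a limited form. The parity rule does not secure the 25/25 split on which power is stated: that split arises about 11% of the time, and 20/30 or worse about 20%. These are exact binomial results that assume only independent draws.

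The consequence for power is small: 0.6 to 0.8 points on average and 2.5 to 3.3 at 18/32. These figures rest on SDs of about 18.2 and 21.0 inferred from the protocol's own error rates; neither is a figure the protocol reports.

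Baseline Barthel is exposed to chance imbalance above 5 points in roughly 3% to 17% of trials, for an assumed SD of 8 to 12.9. The planned ANOVA does not adjust for it. This is a separate matter from arm size and needs its own remedy. The case for acting rests on the inconsistency and the low cost of repair, not on lost power.

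**What to change.** **1. Allocation list.** Replace the parity rule with a restricted list prepared once and concealed from the staff who recruit. There are two options:
- A random permutation of 25 experimental and 25 control labels, which secures 25/25 when all 50 are randomised.
- Permuted blocks of mixed, undisclosed sizes (for example 4 and 6), optionally within two baseline Barthel strata. This secures near-equal arms, not exact equality: each stratum can end in an incomplete block with an excess of at most 3, so two strata could differ by 6 in total, or 22/28.

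**2. Analysis.** Adjust the Barthel analysis for baseline Barthel, by ANCOVA or an equivalent model. The value is already collected before randomisation. This is needed whichever list is used.

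**3. If simple randomisation is kept.** State that arm sizes are random and give power as an average over the possible splits, with the SD used. On the two back-solved SDs that would be 89.4% or 79.2%.

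**Cost.** One newly generated list, a sentence on allocation and a sentence on the model. The downside is some predictability late in the list or block, limited by concealment and, for blocks, by mixed sizes.

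### The stated roles join the allocation sequence to enrolment, no step is described that hides the next allocation from the recruiter, and the bias claim covers more than the separation protects

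*Protocol article*

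**What the plan says.** All of this is in the Protocol article.

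- **Sequence** (Sample/participants, paragraph on assignment, randomisation and blinding). Simple randomisation is done by "generating a table of random numbers of the same size as the estimated study sample with Microsoft Excel 2020". The arm can be read from each entry: "For even numbers, the subject will be assigned to the Experimental Group, and for odd numbers, the subject will be assigned to the Control Group".
- **Roles** (same paragraph). "Randomisation, recruitment and assignment of subjects to each group will be performed by research staff not involved in the evaluations or interventions". The article adds that this is an arrangement "which will avoid potential bias in the study".
- **Invitation** (Sample/participants, opening paragraph). "The Unit’s investigators will invite patients to participate in the study by explaining the details of the clinical trial".
- **Order of steps** (Evaluations and study plan; Baseline visit). Recruitment comes first, then the baseline assessment, then randomisation.
- **Sampling** (Design and aims). Patients are sampled consecutively.
- **Blinding** (Sample/participants; Limitations). Participants are not blinded. Those who measure outcomes and those who analyse the data are.

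**The concern.** Randomisation removes selection bias only if the person deciding whether and when to enrol a patient cannot know the next assignment. Here the full sequence exists beforehand in readable form, and the group that randomises also recruits and assigns. The only separation stated is from assessment and from delivery of the interventions, which bears on later stages of the trial.

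At stake is the comparability of the arms in an open-label, single-unit trial of 50 patients. If a recruiter knew the next arm, fitter or more motivated patients could be approached or timed so that they entered the exercise arm. Blinded assessors would then measure accurately a difference that was present at entry. The planned time-by-group repeated measures ANOVA cannot correct for unmeasured traits such as motivation.

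**Working it through.** **1. What each stated safeguard does at entry.** No figure in the article decides this point, so the statements are compared first.

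| Stated feature | What it protects | Does it hide the next allocation from the recruiter? |
|---|---|---|
| Recruiting and randomising staff take no part in assessment or treatment | Outcome assessment | No |
| Assessors and analysts blinded | Measurement and analysis | No |
| Baseline assessment before randomisation | Baseline scores, if the next arm is unknown | No; the table may already exist |
| Consecutive sampling, numeric eligibility limits (Barthel, asthenia VAS, MMSE, haemoglobin) | Reduces discretion over who enters | No; invitation, timing and consent remain |
| Simple randomisation without blocks | The next arm cannot be deduced from past ones | No; irrelevant if the table can be read |

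No row closes the gap between sequence and enrolment, and the Limitations section discusses only blinding.

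**2. Who recruits.** One paragraph gives invitation to the Unit's investigators. The next gives recruitment to staff outside assessment and treatment. These may be the same people, but the article does not say so. This is an ambiguity, not a proven contradiction.

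**3. Illustration of size.** Inputs from the article: 25 per arm, two-sided alpha 0.05, a 17-point Barthel difference, stated power 90%. No SD is given, so the 90% cannot be reproduced; only the SD it implies can be derived.

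- SD = 17 / [(1.960 + 1.2816) × √(2/25)] = 17 / (3.2416 × 0.2828) = 18.5 (normal approximation; 18.2 with the t distribution).
- The same sentence gives a beta of 0.2. At 80% power: 17 / [(1.960 + 0.8416) × 0.2828] = 21.5.

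Suppose the treatment has no effect, but selection at entry makes the arms differ by b points in expected Barthel change. Then:

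- λ = b / (SD × √(2/25)); with SD 18.54 the denominator is 5.244.
- Type I error = P(|T| > 2.011), where T is noncentral t with 48 degrees of freedom and noncentrality λ.

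| b (assumed) | λ at SD 18.54 | Type I error, SD 18.54 | Type I error, SD 21.45 |
|---|---|---|---|
| 0 | 0 | 5% | 5% |
| 2 | 0.38 | 7% | 6% |
| 4 | 0.76 | 12% | 10% |
| 6 | 1.14 | 20% | 16% |
| 8 | 1.53 | 32% | 25% |

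This uses a two-sample t-test on change with exactly 25 per arm. Simple randomisation will not usually give that split, and the planned analysis is a repeated measures ANOVA, so the table shows order of magnitude only.

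**The case against.** The strongest reply is that the article never says the list is open. The three tasks go to research staff as a group, so they could be split among individuals. A condensed article commonly leaves envelopes, a list holder or an electronic release to the full protocol, and silence on those is no fault. Sampling is consecutive, eligibility is largely numeric, baseline precedes assignment, and unblocked randomisation does not let past assignments reveal the next.

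Much of this stands. A reader might infer that the same individuals generate the table, recruit and assign, that the recruiter always sees the next row, and hence that allocation is definitely unconcealed. The text does not support that: the overlap is at group level, and access to the table is not described either way. A reader might also infer that the bias statement is simply false. It is over-general: the separation does help protect outcome assessment.

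What does not stand is the defence that this is only missing detail. The article states a role arrangement that puts sequence and enrolment in one group, and offers that arrangement as the protection against bias. The partial safeguards reduce the opportunity for selection, but none hides the next allocation.

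**Conclusion.** The point holds in limited form. As stated, the roles join sequence and enrolment, no concealment step is described, and the claim about avoiding bias goes beyond what separation from assessment and treatment can deliver. The documents do not show that selection would occur or how large it would be. Assuming SDs of 18.5 to 21.5 and shifts of 2 to 8 Barthel points, the type I error would be about 6% to 32% instead of 5%; both the SD and the shift are assumptions. The matter should be settled before enrolment, since analysis cannot fully undo selection at entry.

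**What to change.** 1. Have an existing team member with no part in recruitment, outcome assessment or statistical analysis generate and hold the list. It should not sit with the statisticians, because the article says those who analyse the data are blinded.
2. Release each allocation only after consent, eligibility and baseline are recorded, by sequentially numbered opaque sealed envelope or an electronic tool.
3. Reword the sentence on roles accordingly, and limit the bias statement to outcome assessment, which the separation does help protect.
4. State whether the Unit's investigators who invite patients are the research staff named in the randomisation paragraph.

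The cost is 50 envelopes or an electronic allocation tool, a change of wording and minor administrative work. Sample size, visits and analysis are unchanged.
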